## 9.3 POPULATIONS FOR ANALYSES

Intention to Treat (ITT) Analysis Population: All enrolled participants

Per-protocol Analysis (see exploratory analyses): All participants who received sufficient 'dose' of the program

## 9.4 STATISTICAL ANALYSES

### 9.4.1 GENERAL APPROACH

Generalized linear mixed models will be used to account for the correlation among youth from the same cluster as well as the correlation between observations from the same youth. Descriptive statistics will be used to summarize the sample with regard to baseline characteristics of interest. Means and standard deviations will be presented for continuous variables, while sample proportions will be provided for categorical variables. 95% confidence intervals will accompany all sample statistics. Primary assessment of intervention effects will be based on intent-to-treat estimates. As-treated, or treatment-on-the-treated (TOT), effect parameters will be estimated in secondary analyses and reported as exploratory. Between-site differences regarding intervention effects will be assessed based on level of staff/facilitator engagement in curricular delivery as well as other observed external factors that may interact with the intervention to alter outcomes. SAS software will be used for all statistical analyses.

To assess differences at baseline between the youth in the experimental and control groups, demographics such as grade-level, race, nativity, and parental education will be compared while accounting for within-neighborhood clustering. Demographic variables as well as neighborhood-level characteristics resulting in between-arm imbalances will be considered as covariates in the primary and secondary analyses.

Participation bias will be assessed by comparison of age and race/ethnicity of youth participating in the study compared to the overall demographics of adolescents (school district and census data). Significant differences detected via chi-square analysis will be noted as potential validity threats.

An attrition analysis will be conducted by comparing youth who completed follow-up surveys with those who did not with regard to demographics as well as outcomes measured at baseline. All hypotheses will be two-sided tests with a significance level of 5%.

Missing data were minimized as much as possible by keeping the surveys as short as possible to reduce survey burden, encouraging youth to be as complete and honest as possible by ensuring anonymity of the surveys, and working assiduously with community partners to ensure that youth stay engaged and can be tracked to complete follow up surveys. Mechanisms for missing data will be investigated by comparing important covariates between youth with and without missing data at each time point. We will characterize these mechanisms as 1) missing completely at random (MCAR), 2) missing at random (MAR), or not missing at random (NMAR). If the nature of our missing data is ignorable (either MCAR or MAR), we will utilize imputation methods such as multiple imputation via chained equations (MICE) to handle dropout. Ultimately, sensitivity analyses will be conducted comparing the results of our imputation methods to complete-case and available-data analyses.

---

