### 5.5 STRATEGIES FOR RECRUITMENT AND RETENTION

*Study setting*

This study involves 20 neighborhoods and 21 clusters in the Pittsburgh area; within each neighborhood, one to four different community partner organizations (referred to as “community

partners” here) participated. Neighborhoods were recruited by identifying a potential community partner who could host the program and were willing to be randomized to receive the intervention or control programming. These community partners included youth-serving organizations, YMCA, Urban League, faith-based organizations, and libraries. Additionally, we partnered with the county’s community intensive surveillance program, a diversion program for youth involved in the juvenile justice system.

Neighborhoods were identified based on having sites where the YMCA, Urban League, or other youth serving partners had existing programs and which were considered lower income communities based on census information and school district data. Asset maps were created for each neighborhood with the goal of identifying community champions and youth-relevant resources to support this community-based project. The strong partnerships established with key stakeholders in each of these sites (including site coordinators, facilitators, and community members) facilitated recruitment and retention as described below.

Among the 20 participating neighborhoods, the proportion of students attending public high schools in those neighborhoods considered economically disadvantaged ranges from 32-100%; the high school graduation rate for those same school districts ranged from 63-97%. Each of these neighborhoods struggle with poverty, school ‘push-out’ (disciplinary actions that push youth, especially African American boys, out of the regular school system), and among the highest rates of gang and gun violence in the county (see Table 2 for neighborhood characteristics). These characteristics were compared by treatment arm using Kolmogorov-Smirnov two-sample exact tests due to their non-normal distributions. Neighborhood characteristics did not vary between the intervention and control arm neighborhoods.

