Within the 20 participating neighborhoods, there were a total of 40 sites/community partners/locations approached and 38 agreed to participate. The composition of the participating sites included 11 places of worship, 20 community centers, 2 public libraries, and 5 juvenile justice community intensive surveillance program centers. One site (cluster) was located at the downtown Urban League office and consisted of youth involved in an African American young men’s leadership group who came from several different neighborhoods and schools in the Pittsburgh area.

For recruitment of eligible youth, we rely on this network of community partners identified in asset maps created for each neighborhood cluster. This includes site leaders, program facilitators, recruiters with strong connections to their community, prevention specialists embedded in schools, school districts that offer community-based programs as an alternative to suspension, and the Community Intensive Supervision Program (CISP) for youth involved in the juvenile justice system.

Using respondent driven sampling (RDS), former and current participants may refer their friends to the program. Participants interested in RDS receive a packet of information on how to recruit a friend or neighbor and five recruitment coupons. When newly-recruited participants come to their first session and turn in their recruitment coupon, the peer recruiter is compensated \$5, up to \$25 overall.

Once community partners recruit youth, retention throughout the 18-hour curriculum is a key focus. Upon enrolling in either the control or experimental arm, prospective participants receive program information, sign an assent form and complete a contact information sheet. Research assistants ensure that the document is legible and that all fields are completed. Research assistants use this information to contact the participant prior to each session to remind them of the session. If youth are not present at the beginning of a session, research assistants and facilitators will contact the participant to encourage them to join late.

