### 6.3 MEASURES TO MINIMIZE BIAS: RANDOMIZATION AND BLINDING

#### Assignment of Interventions

##### Randomization

Randomization was performed at the neighborhood level (i.e., cluster) to reduce risk for contamination. The initial randomization included 10 clusters that were assigned to experimental or control conditions. The study statistician performed this randomization, stratifying by lead site in that neighborhood (YMCA, Urban League, or Other), such that within each stratum, each site/neighborhood had a 50/50 chance of being assigned to intervention or control. Due to a combination of lower-than-expected recruitment by neighborhood (target=96 participants each) and the interest from other community partners, we individually randomized an additional 11 neighborhoods, stratified by type of site. This resulted in a total of 21 clusters randomized, with 11 assigned to experimental and 10 assigned to control. All neighborhoods in the study met the original criteria of being socially or economically disadvantaged and/or predominantly African American.

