##### Blinding

Randomization was performed after approval for the study was obtained for a site in a new neighborhood so that the randomization assignment would not influence a site's willingness to participate. Notably, the PI was blinded from randomization until she had successfully recruited a site to participate in the study. Due to the study design, investigators, research staff, community partners, facilitators, and youth participants could not be blinded to study assignment.

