#### 9.4.2 ANALYSIS OF THE PRIMARY ENDPOINT(S)

The primary outcome for this study is reductions in self-reported perpetration of SV and ARA at Time 3, compared to controls. We will examine whether Manhood 2.0 results in improvements in the primary outcome assessed at 9 months after end of program (Time 3) compared to controls. Generalized linear mixed models will be used and will include variables for baseline SV/ARA perpetration, treatment group, and random effects for cluster.

---

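### Additional covariates for the primary model are chosen by observed arm imbalance, the randomization strata are left out, and neighborhood balance is inferred from non-significant tests on about 20 units

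*Protocol*

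**What the plan says.** **Fixed terms.** Protocol section 9.4.2 says that the primary models "will include variables for baseline SV/ARA perpetration, treatment group, and random effects for cluster". These terms stand whatever the balance between arms.

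**Additional covariates.** Section 9.4.1, repeated in 9.4.5, first compares youth demographics between arms, allowing for clustering, and then states: "Demographic variables as well as neighborhood-level characteristics resulting in between-arm imbalances will be considered as covariates in the primary and secondary analyses". The demographics are given as examples. No size of difference or p-value is set as the trigger.

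**Randomization.** Sections 4.1 and 6.3 describe two batches. The first 10 clusters were stratified by lead site (YMCA, Urban League or Other). A further 11 were stratified by type of site. "This resulted in a total of 21 clusters randomized, with 11 assigned to experimental and 10 assigned to control". Neither stratification appears among the model terms in 9.4.2.

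**Neighborhood balance.** Section 5.5 says: "These characteristics were compared by treatment arm using Kolmogorov-Smirnov two-sample exact tests due to their non-normal distributions". It concludes: "Neighborhood characteristics did not vary between the intervention and control arm neighborhoods". The number of units per arm in these tests is not stated. The same section says "This study involves 20 neighborhoods and 21 clusters" and explains "One site (cluster) was located at the downtown Urban League office", with youth drawn from several neighborhoods.

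**Enrolment.** Under section 5.1 the program on offer is already settled by neighborhood when a youth agrees to take part. Section 6.3 adds that "youth participants could not be blinded to study assignment".

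**The concern.** A covariate helps the primary analysis when it predicts the outcome. An imbalanced variable that does not predict perpetration adds only noise. A strong predictor that happens to look balanced is still worth including. A rule that starts from imbalance therefore picks on the wrong property. Because the rule has no threshold and no list, two analysts following 9.4.1 faithfully could fit different primary models, each settled after the arms had been compared.

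Two features of this trial raise the stakes. First, clusters were randomized but youth enrol knowing the program, so the mix of enrollees can differ between arms for reasons that randomization does not control. Prespecified adjustment for prognostic variables is the practical safeguard. Second, the randomization was stratified, and the model does not carry the strata.

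The statement in 5.5 is a separate weakness. Having declared that neighborhood characteristics do not differ, the protocol gives a reader no reason to expect any neighborhood term in the model, yet the declaration rests on a test with little ability to find a difference.

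**Working it through.** **1. What is fixed and what is open**

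| Term | Where | Status |
|---|---|---|
| Baseline SV/ARA, treatment, random cluster effect | 9.4.2 | Fixed |
| Demographics | 9.4.1, 9.4.5 | Considered if imbalanced; no threshold or closed list |
| Neighborhood characteristics | 9.4.1, 9.4.5 | Same |
| Randomization stratum (lead site, type of site) | 4.1, 6.3 | Not named in the model |

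**2. What the K-S tests could detect.** The protocol gives no power for these tests, so there is no stated figure to reproduce. Inputs: 11 and 10 clusters (6.3) and a two-sided 5% level (9.4.1). Shape and shift are assumptions, because 5.5 gives no distributions beyond calling them non-normal.

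The exact null distribution for 11 against 10 rejects when the statistic is at least 0.545, a true size of 4.3%. Simulated power:

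| Shift (SD) | Normal | Uniform | Exponential |
|---|---|---|---|
| 0.5 | 14% | 12% | 32% |
| 0.8 | 31% | 25% | 65% |
| 1.0 | 46% | 38% | 80% |

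For normal values, 80% power needs a shift of about 1.5 SD. If the tested units were the 20 neighborhoods, power at 0.8 SD (normal) is 27% for 11 against 9 and 14% for 10 against 10. The last figure is so low because the exact test's true size there is only 1.2%.

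**3. How often chance produces such imbalance.** For one characteristic, the standard error of the difference in means is sqrt(1/11 + 1/10) = 0.437 SD. A realised difference above 0.5 SD then has probability about 25% (0.5/0.437 = 1.14), and above 0.8 SD about 7% (0.8/0.437 = 1.83). Simulating 200,000 randomizations with normal values, a realised difference of at least 0.8 SD that also escapes the K-S test occurs in 4.2% of trials, and one of at least 1.0 SD in 0.9%.

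**4. What an unadjusted imbalance could do.** Inputs from 9.2: ICC 0.01, a 20% rate, 866 youth, 80% retention, an 8.3-point target. Shift in risk = imbalance × sqrt(f × ICC × p(1−p)), where f, the share of between-cluster variance explained, is an assumption. At 0.8 SD:

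- f = 0.5: 0.8 × sqrt(0.5 × 0.01 × 0.16) = 2.3 points, or 27% of 8.3
- f = 1: 0.8 × sqrt(0.01 × 0.16) = 3.2 points, or 39% of 8.3

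For scale, 866 × 0.8 / 21 = 33.0 youth per cluster, and the design effect is 1 + 32.0 × 0.01 = 1.32. Effective sizes are 11 × 33.0 / 1.32 = 275 and 10 × 33.0 / 1.32 = 250. The standard error of the arm difference is sqrt(0.16 × (1/275 + 1/250)) = 3.5 points. Both shifts lie within one standard error.

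The 8.3 points serve only as a yardstick. After 80% retention the detectable difference recomputes to 8.8 points, and to 8.2 if all 866 are analysed. That is a separate matter and does not bear on this point.

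**The case against.** **The strongest prognostic variable is probably already in.** A reader might infer that covariates enter only when an imbalance is found. Section 9.4.2 rules that out: the baseline outcome is always included. This stands and limits the point to the additional covariates.

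**The K-S test is not the screen.** It is tempting to say that important imbalances will be dropped because a weak K-S test fails to flag them. No section makes K-S, or any p-value, the entry criterion. Demographics are compared at youth level under 9.4.1, where the powers above do not apply. The K-S tests concern area characteristics, which do not change with who enrols. This stands, so the wording in 5.5 and the selection rule are separate faults.

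**The power figures depend on shape.** Section 5.5 calls the distributions non-normal, and for a strongly skewed shift power at 0.8 to 1.0 SD is 65% to 80%. This also stands: the test is weak for symmetric shapes and moderate for strongly skewed ones.

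**The 2.3 points are not systematic bias.** Neighborhoods were randomized, so an imbalance in their characteristics is chance, already allowed for by the ICC and the random cluster effect, and further reduced by the baseline outcome term. This stands.

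**The covariate list may be in a separate analysis plan, and the rule looks at baseline data, not outcomes.** Nothing in the protocol says that Time 3 results by arm guide the choice, and that should not be inferred. But the protocol does not simply defer the matter. It states a selection rule, and a later list built on that rule would inherit the wrong criterion. This objection fails.

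**Conclusion.** The point holds in a limited form. Beyond baseline SV/ARA, sections 9.4.1 and 9.4.5 select covariates by observed imbalance with no threshold or closed list, so the primary model is not settled until arms have been compared. The stratification used in randomization is missing from the model. Enrolment after the program is known makes a fixed prognostic set more valuable here than in an individually randomized, blinded trial.

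Separately, the conclusion in 5.5 overreads non-significant tests on about 20 units. The support is the detection rate at 0.8 SD of 31% (normal), 25% (uniform) or 65% (exponential), assuming 11 against 10 units; the true units are not stated.

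The likely numerical effect is modest. A large unflagged imbalance in any one neighborhood characteristic is uncommon (4.2% at 0.8 SD or more, normal values), though several characteristics raise the overall chance. Its effect of 2.3 to 3.2 points, under the assumed f of 0.5 to 1, is within one standard error of the arm difference. The case for change rests mainly on fixing the primary model in advance and only secondarily on these magnitudes. The change should be made.

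**What to change.** - **Sections 9.4.1 and 9.4.5:** replace the imbalance sentence with a short adjustment set, fixed before Time 3 outcomes are viewed by arm: baseline SV/ARA as already planned, age, and the site-type randomization stratum. State one coding of the stratum that covers both randomization batches. Capture juvenile-justice site within that coding or as one added term. Align 9.4.2 with the list.
- **Sensitivity analysis:** keep the imbalance-selected model here, labelled as such.
- **Section 5.5:** replace the statement of no difference with the observed differences by arm, and state the number of units per arm.

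**Cost.** No new data are needed. Age takes 1 degree of freedom, a three-level stratum 2, and a separate juvenile-justice term 1, so 3 to 4 in all. The stratum terms sit at cluster level, where 21 clusters in two arms leave 21 − 2 = 19 degrees of freedom, falling to 17 with a three-level stratum. Coding takes some work, because the two batches describe their strata differently and the 38 participating sites are spread over 21 clusters, so one cluster can hold more than one type of site.

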#### 9.4.2 ANALYSIS OF THE PRIMARY ENDPOINT(S)

The primary outcome for this study is reductions in self-reported perpetration of SV and ARA at Time 3, compared to controls. We will examine whether Manhood 2.0 results in improvements in the primary outcome assessed at 9 months after end of program (Time 3) compared to controls. Generalized linear mixed models will be used and will include variables for baseline SV/ARA perpetration, treatment group, and random effects for cluster.

---

#### 9.4.3 ANALYSIS OF THE SECONDARY ENDPOINT(S)

For positive bystander intervention (secondary outcome) and the remaining additional outcomes, the models will include variables for the secondary outcome at baseline, treatment group, and random effects for cluster. This will allow us to assess the effect of the study arm after accounting for clustering within neighborhoods. As an exploratory analysis, all three time points will be included in a single generalized linear mixed model to quantify the long-term trajectories of each of the secondary outcomes.

Following Twisk and Proper's recommendations for randomized controlled trials with both baseline and follow up measures (in this case abuse perpetration),(51) we will also construct multinomial logistic regression models that account for presence or absence of baseline perpetration. That is, we will examine intervention effects among youth reporting baseline SV/ARA perpetration and the likelihood of becoming 'non abusive' at follow up (i.e., an 'early intervention' effect). Similarly, we will examine intervention effects among youth with no baseline SV/ARA perpetration and the likelihood of 'staying non abusive' (i.e., a primary prevention effect). We have used this approach to analyze intervention effects on abuse exposure in our school health center relationship abuse prevention study.(52)

---

#### 9.4.4 SAFETY ANALYSES

N/A

---

#### 9.4.5 BASELINE DESCRIPTIVE STATISTICS

To assess differences at baseline between the youth in the experimental and control groups, demographics such as grade-level, race, nativity, and parental education will be compared while accounting for within-neighborhood clustering. Demographic variables as well as neighborhood-level characteristics resulting in between-arm imbalances will be considered as covariates in the primary and secondary analyses.

---

#### 9.4.6 PLANNED INTERIM ANALYSES

N/A

---

#### 9.4.7 SUB-GROUP ANALYSES

Participation bias will be assessed by comparison of age and race/ethnicity of youth participating in the study compared to the overall demographics of adolescents (school district and census data). Significant differences detected via chi-square analysis will be noted as potential validity threats.

An attrition analysis will be conducted by comparing youth who completed follow-up surveys with those who did not with regard to demographics as well as outcomes measured at baseline. All hypotheses will be two-sided tests with a significance level of 5%.

---

#### 9.4.8 TABULATION OF INDIVIDUAL PARTICIPANT DATA

N/A

---

#### 9.4.9 EXPLORATORY ANALYSES

We will also conduct two sets of exploratory analyses. First, we will conduct an intensity-adjusted analysis that reflects the actual delivery of the program. To achieve this, we will use a continuous score of “intensity” to replace the binary intervention variable in the models for the primary analysis. This score will be calculated for each round (program delivery) by using two sources of information. The first is information collected systematically about each session by trained research assistants who observed the sessions, including whether each task assigned to a module was performed (yes or no). The second is a summary measure of overall attendance for each round, tracked by using sign-in sheets with the research assistants. The second set will be a per-protocol analysis. This set of models will include only participants in the intervention arm that received the full intervention, defined as having covered a minimum threshold of tasks across the six sessions and having sufficient attendance. These measures replicate the intensity score values, but are then dichotomized to yes or no to receiving the full intervention. All control arm participants will be included in these models.

To explore whether demographics, youth pre-intervention risk and protective factors (e.g., history of SV/ARA exposure, sexual risk, connectedness), and site-level differences (e.g., staff experience, organizational capacity, intervention intensity) moderate the effect of the intervention on the primary and secondary outcomes, linear mixed models slightly different from those described above will be utilized. The outcome variables will be modeled as a function of the following variables: the outcome at baseline, the treatment group, the potential moderator, the interaction between the treatment group and moderator, and a random effect for cluster. A significant interaction suggests the presence of intervention effect heterogeneity, and we will follow the approach of Kraemer (53) by focusing on effect size derivation rather than formal hypothesis testing.

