## 6 STUDY INTERVENTION(S) OR EXPERIMENTAL MANIPULATION(S)

### 6.1 STUDY INTERVENTION(S) OR EXPERIMENTAL MANIPULATION(S) ADMINISTRATION.

#### 6.1.1 STUDY INTERVENTION OR EXPERIMENTAL MANIPULATION DESCRIPTION

##### **Experimental and Control Arms:**

Program Delivery: Both experimental and control arm interventions involve 18 hours of curriculum, generally spread out over 3 to 6 week periods. The program is delivered with some variation in schedules to meet the needs of community partners and participating youth. Such configurations include but are not limited to: three 6-hour sessions spanning three weekdays during the summer (for job skills training only), nine 2-hour sessions held twice per week on weekday evenings, and six 3-hour sessions held once or twice per week on weekday evenings or Saturday afternoons (which was the preferred and most commonly used design).

Fidelity to intervention: For both intervention and control arms, research assistants are present at every session to track attendance, facilitate program implementation logistics (such as ordering food), and to complete detailed fidelity forms that assess facilitators' ability to deliver the content of the program as intended.

**Manhood 2.0 (experimental arm):** Manhood 2.0 guides youth to explore and reflect upon social constructions of masculinity, describe healthy relationships, discuss healthy sexual behaviors, identify coercive and disrespectful behaviors, and practice skills to intervene when witnessing peers' disrespectful and harmful behaviors, with repeated reflection on gender norms throughout these sessions. The curriculum involved three main topic areas. The first focuses on the theme of gender, masculinity and power, allowing the young men to actively reflect on the messages and expectations that they have received from society about manhood and gender norms. The second topic focuses on the theme of violence. This includes several components: an exploration of the various forms of violence, its impact on communities, and the role that masculinity may contribute; identifying healthy versus unhealthy romantic relationships; sexual consent and decision making; and bystander interventions when witnessing abusive behavior. The final topic area focuses on sexual and reproductive health, which includes providing

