### 6.1.2 ADMINISTRATION AND/OR DOSING

**Tracking Dosage:** Attendance forms are completed at each site for each round. As surveys are anonymous, tracking number of sessions for each individual is not feasible. Thus, dosage will be calculated for each round based on % overall attendance.

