### **Main Study Phase:**

**Baseline survey:** Youth are asked to complete the baseline survey the first time they attend a session (can enter study at Sessions 1 – 3; if participant is interested in joining, they are asked to return for the next round). All sites conduct web-based surveys (back up paper surveys are used as needed) on tablets using REDCap, an online data management and survey system. Responses to the anonymous web-based secure survey are entered by the youth participants themselves on an electronic tablet; no data are stored on the computers themselves. Only research staff who have been added to the project can access this online database. Data are downloaded and stored on a password-protected share drive that can only be accessed by users with the appropriate permissions. No names are connected to the survey data as each participant creates their own secret code as described above.

**End of program survey:** At the end of the program, youth are asked to complete an end of program survey that asks about which sessions they attended, their impressions of the program, as well as some additional school and community related questions (about connectedness to school, suspensions, social supports, important adults). Surveys are self-administered on electronic tablets provided by the research staff (back up paper surveys will be used if tablets are not available or fail). All participants, regardless of amount of curriculum completed, are eligible to take this survey; participants are asked to complete the end of program survey later if they miss the last session.

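### The exploratory per-protocol analysis filters only the intervention arm, and by round, although the linked end-of-program survey records which sessions each youth attended

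*Protocol*

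**What the plan says.** Section 9.4.9 of the protocol plans two exploratory sets of models: one replaces the treatment indicator with a continuous intensity score, the other is per-protocol. For the second, "This set of models will include only participants in the intervention arm that received the full intervention", which means a minimum coverage of tasks over the six sessions plus sufficient attendance. The control arm is not filtered: "All control arm participants will be included in these models".

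The unit of the filter is the round. On the intensity score, section 9.4.9 says "This score will be calculated for each round (program delivery) by using two sources of information", and on the per-protocol criteria "These measures replicate the intensity score values, but are then dichotomized to yes or no to receiving the full intervention". Section 6.1.2 likewise sets dose as the round's overall attendance percentage because, with anonymous surveys, "tracking number of sessions for each individual is not feasible".

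Other sections describe the available data differently. Section 6.1.1: "For both intervention and control arms, research assistants are present at every session to track attendance", and the same staff complete fidelity forms in both arms. Section 8.1, on the end of the program: "youth are asked to complete an end of program survey that asks about which sessions they attended". Section 8.1 also says that all surveys are linked by a personal code that the youth generates.

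Section 9.3 gives the per-protocol set as all participants who had enough of the program, with a pointer to the exploratory analyses and no mention of arm.

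**The concern.** Attendance and task coverage arise after randomisation. Filtering one arm on them and leaving the other whole compares a selected subset of intervention rounds with an unselected control arm. If rounds with good attendance differ from the rest in site, facilitator or underlying risk of the youth, a difference appears even when the program does nothing.

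Separately, a round-level label does not describe the participant. Section 8.1 says a youth "can enter study at Sessions" 1 to 3. In the six-session format, which section 6.1.1 calls the most common, a youth who joins at session 3 can attend at most 4 of 6 sessions, yet he counts as fully treated if his round qualifies. A youth with complete attendance in a poorly attended round is dropped. The data that could correct this at participant level are already collected.

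At stake is how a positive per-protocol result would be read: as evidence that the program works when properly delivered, when it might reflect which rounds were kept.

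**Working it through.** **1. The passages side by side**

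| Question | Sections 9.4.9 and 6.1.2 | Elsewhere in the protocol |
|---|---|---|
| Who is filtered? | Intervention arm only | 9.3: all participants with enough dose, no arm exempted |
| At what level? | Round | 9.3: participant |
| Is control attendance known? | Not used | 6.1.1: tracked at every session in both arms |
| Is individual attendance known? | Said to be infeasible | 8.1: self-reported by session at end of program, linked by code |

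Section 6.1.2 is right about the sign-in sheets, which carry identities that the anonymous surveys do not. It overlooks the survey item, which is inside the linked data.

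**2. How large could the selection effect be?**

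The protocol gives no figure to reproduce here. Input from the documents: a 20% perpetration rate (section 9.2). Assumed inputs: no true program effect; round attendance z standard normal; logit(risk) = a + ln(OR) × z, with a set so that mean risk is 20%; OR per SD of attendance from 0.9 to 0.6; best-attended 80%, 60% or 40% of intervention rounds kept, against all controls.

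Spurious reduction = 20% − mean risk in the rounds kept, in percentage points:

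| OR per SD | 80% kept | 60% kept | 40% kept |
|---|---|---|---|
| 0.9 | 0.6 | 1.1 | 1.6 |
| 0.8 | 1.3 | 2.3 | 3.4 |
| 0.7 | 2.1 | 3.7 | 5.2 |
| 0.6 | 3.1 | 5.2 | 7.3 |

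A hand-checkable case within this range: if the better-attended half of rounds has 16% and the rest 24%, the arm average is (16 + 24)/2 = 20%, and the contrast is 20 − 16 = 4 points. For scale, section 9.2 gives a detectable difference of 8.3 points. If the association ran the other way (OR above 1), the sign would reverse. None of these figures includes the baseline-perpetration covariate.

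**3. How many youth could be mislabelled?**

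Assume a six-session round with 80% mean attendance. X is the number of sessions attended by one youth.

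- Binomial(6, 0.8): P(X = 6) = 0.8^6 = 0.262; P(X = 5) = 6 × 0.8^5 × 0.2 = 0.393; so P(X ≤ 4) = 1 − 0.262 − 0.393 = 0.345, and P(X ≤ 3) = 0.099.
- Beta-binomial, same mean, within-youth correlation 0.3: P(X ≤ 4) = 0.316 and P(X ≤ 3) = 0.192.
- Binomial with 90% attendance: P(X ≤ 4) = 0.114.

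The share is 32 to 35% if 5 of 6 sessions are needed and 10 to 19% if 4 of 6 suffice, both at 80% attendance; it falls to 11% for the stricter rule at 90% (binomial). The protocol states neither the cut-off nor the expected attendance, so no single figure can be assigned.

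**The case against.** The strongest replies, and what remains of each:

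- **The analysis is exploratory.** True. Section 9.4.1 bases the primary assessment on intention to treat and reports as-treated effects as exploratory. This limits the weight of the point but does not answer it.
- **The direction of bias is not shown.** This stands. A reader might infer that the bias must favour the intervention. No section links round attendance to perpetration risk. Section 5.5 describes recruitment through a juvenile-justice supervision program and alternatives to suspension; if supervised youth attend well and carry higher risk, selection would work against the intervention.
- **Baseline adjustment may absorb part of it.** This stands in part. The primary model in section 9.4.2 includes baseline perpetration, and imbalanced covariates are to be considered. If the per-protocol models inherit these terms, the table overstates what remains. Section 9.4.9 does not say that they do, and differences in site or facilitation would not be fully removed.
- **The cut-off may be set elsewhere.** Agreed, so a claim that about a third of youth would be mislabelled is not supported. The 4-of-6 ceiling for late joiners also applies only to six-session rounds; in the nine-session format, entry at session 3 still allows 7 of 9.
- **Observed round attendance may be better than self-report.** It is a defensible choice. The survey item is retrospective and missing for non-responders, and relying on respondents alone could itself select on engagement.
- **Controls receive none of the intervention at any attendance, and parallel thresholds would not restore randomisation.** Both are correct. Parallel criteria remove the one-arm filter, not all selection, because the curricula and some schedules differ. This is why an instrument-based estimate is preferable.
- **Section 9.3 defers to 9.4.9.** It does carry a pointer, so the mismatch may be shorthand. The two texts still describe different sets and should agree.

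**Conclusion.** The point holds in a limited form. As written, section 9.4.9 yields a non-randomised contrast by filtering one arm on post-randomisation, round-level criteria, and it does not match section 9.3. The reason in section 6.1.2 for not using individual dose is incomplete, because linked self-reported attendance is collected.

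The size is uncertain. Under the stated assumptions the spurious benefit ranges from 0.6 to 7.3 points before baseline adjustment. It depends on an attendance–risk association and a share of rounds kept, neither of which the protocol gives, and the sign could be the opposite. The mislabelled share depends on an unstated cut-off.

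A reader might also infer that the trial's main result is compromised. It is not: the primary intention-to-treat analysis uses none of these criteria. The change is worth making but is not critical.

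**What to change.** 1. **Sections 9.4.1 and 9.4.9.** Make the treatment-on-the-treated (complier-average) estimate already named in 9.4.1 the main dose analysis, with randomised arm as the instrument and clustering accounted for. Take individual dose from the linked end-of-program session items. Keep round-level attendance and fidelity as descriptors, and as auxiliary information for youth without an end-of-program survey. State the assumption that assignment acts on the outcome only through the dose.
2. **Sections 9.3 and 9.4.9.** If a per-protocol set is kept, give it one definition in both places, apply parallel attendance and task criteria to both arms, adjust for baseline perpetration, and label the result as a non-randomised comparison.
3. **Section 6.1.2.** Say that the sign-in sheets cannot be linked to individuals, but that self-reported attendance by session can.

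Cost: wording and modest programming, with no new data. The downsides are that attendance is self-reported and missing for end-of-program non-responders, and that some selection remains in any per-protocol set.
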